## Duration of Therapy

Use of nasal spray will last for 3 days in-patient treatment, followed by 4 weeks outpatient treatment.

Subjects may also discontinue protocol therapy in the following instances:

- Intercurrent illness which would in the judgment of the investigator effect patient safety, the ability to deliver treatment or the primary study endpoints.
- Self-reported or observed side-effects or adverse effects.
- Request by patient.

## Premedication and Monitoring

CIWA-Ar with blood pressure and heart rate monitoring are to be assessed as usual, frequency or change of monitoring necessary. See appendix B.

## Concomitant Medication

The following medication is not allowed while the patient is included in the study:

Restriction applies to chronic use.

- Any kind of benzodiazepines: Alprazolam (Xanor), Diazepam (Vival, Stesolid), Flunitrazepam (Rohypnol), Lorazepam (Temesta), Nitrazepam (Mogadon, Apodorm), Oxazepam (Sobril), Klonazepam (Rivotril), Triazolam (Halcion), benzodiazepine-like medication and z-hypnotica: Zolpidem (Stilnoct), Zopiklone (Imovane, Zopiclone).

All concomitant medication (incl. vitamins, herbal preparation and other “over-the-counter” drugs) used by the patient will be recorded in the patient’s file and CRF. At discharge, the patient will receive a notebook dated with the dates for next 4 weeks; one day per page. Here, time and dosage (including any changes of dosages) of any concomitant medication or herbal product etc. ingested will be filled in. The patient cannot participate concomitantly in another medical clinical trial. All medication will be administered to in-patients which will ensure that the study’s restrictions on use and dosages are followed, and that any adverse effect is registered in the CRF.

## Subject Compliance

Procedures for determining compliance with medications at in-patient setting will be observed by staff. Nasal spray administration 2 hours prior to or 2 hours after scheduled is not considered a deviation from compliance or time schedule. This could happen e.g. if patients are sleeping, as patients will not be awakened if they are sleeping. Nasal spray will be weighed when patients return for their last visit after 4 weeks, to estimate use. The last visit (day 30) will take place in the period day 28 -32, as close to day 30 as practically feasible. Also, the patient will receive a notebook in which the date, time and dosage of nasal spray use, use of concomitant medication and alcohol intake during the 4 weeks after discharge should be noted. The patients will also receive a follow-up phone call 1 week after discharge.

## Drug Accountability

The responsible site personnel will confirm receipt of study drug, and also keep track of number of bottles in use in a form which is kept locked inside the medicine cabinet, and will use the study drug only within the framework of this clinical study and in accordance with this protocol.

In-patients will be given drug or placebo nasal spray twice daily by nurses.The nasal spray will be kept in a medicine cabinet whenever not used and will be administered to the patients. The batch number will be noted in the CRF of the patients. Any deviation from the planned dosage is also noted in the CRF.

Outpatients will have nasal spray available at home. The number of bottles and the batch number(s) given to each patient will be noted in the CRF. When patients come back for follow-up interview, the containers will be returned to Lade Addiction Treatment Center after weighing. Lade Addiction Treatment Center will follow standard hospital procedure for destruction after use.

## Drug Labeling

The investigational product will have a label permanently affixed to the outside and will be labeled according with ICH GCP and national regulations, stating that the material is for clinical trial / investigational use only and should be kept out of reach of children.

Labels will be written in Norwegian. There is one label for in-patient use, another label for use at home. See appendix D.

## Subject Numbering

Each subject is identified in the study by a unique subject number that is assigned when subject signs the Informed Consent Form. Once assigned the subject number it cannot be reused for any other subject. The same primary identifier is used throughout the study.

The study treatment will be administered to the subject by nurses only when admitted for in-patient treatment. As outpatients the treatment will be dispensed to subjects.

# STUDY procedures

## Flow Chart

Table 1. Trial flow chart

|  | **In-patient period (day)** | | | **Outpatient Period (day)** | |
| --- | --- | --- | --- | --- | --- |
| **Time** | **On arrival**  **D 1** | **D 2** | **Discharge**  **D 3** | **D 30** | **D 60** |
| Informed consent | X |  |  |  |  |
| Inclusion/exclusion  Evaluation | X |  |  |  |  |
| Medical History, record of concomitant medication | X |  |  | X |  |
| Prior treatment | X |  |  |  |  |
| Physical Examination^1)^ | X |  |  |  |  |
| Vital signs, CIWA-Ar ^2)^ | X | X | X | X |  |
| Blood samples^3)^ | X |  | X | X |  |
| Urine samples^4)^ | X |  | X | X |  |
| Actigraph | X | X | X |  |  |
| Staff administered nasal spray | X | X | X |  |  |
| Self-reported sleep | X | X | X | X |  |
| Alcohol Craving Experience Questionnaire(ACE), SCL-10, PAM-13^5)^ |  |  | X | X |  |
| RMET^6)^, dot-probe-task^7)^ |  | X | X | X |  |
| Self-administered and reported use of nasal spray, relapse to drinking and weighing of spray bottles |  |  |  | X |  |
| Alcohol consumption (Time-Line Follow-back^8)^, Days until relapse, Daily quantity of standard alcohol units, Number of binge drinking episodes, self-reported intake of benzodiazepines |  |  |  | X |  |
| Phone interview with AUDIT^9)^ |  |  |  |  | X |

1. Cor/pulm/abdomen and peripheral lymph node status and neurology with emphasis on alcoholic damage to the cerebellum and signs of Wernicke/Korsakoffs syndrome.
2. Blood pressure, pulse, temperature, weight, alcohol expiration test until 0‰ x 2. CIWA-Ar after symptom driven protocol
3. Once daily: CRP, Hb, HCT, WBC (incl.differential counting, Na, K, Ca, glucose, creatinine, ALAT, LD, ALP, γGT, INR, albumin, bilirubin, p-oxytocin, CDT, PEth.
4. Once daily: Toxicology screening: urine dipstick and laboratory tests (incl. the ethanol metabolites EtG and EtS. (Pregnancy test (HCG) at admittance in fertile women).
5. See chapter 7.3 Other assessments
6. See chapter 7.3 Other assessments
7. See chapter 7.3 Other assessments
8. See chapter 7.3 Other assessments
9. See chapter 7.3 Other assessments

## On arrival

**Informed consent**

Informed consent must have been given voluntarily by each subject that meets the inclution and exclution criterias before any study specific procedures are initiated.

The following tests will be done at screening at admittance:

**Clinical status**

See Table 1. This physical check-up is standard procedure for all patients admitted at Lade Behandlingssenter and includes a physical examination, vital signs and history taking of alcohol intake and prior illnesses.

**Concomitant medication**

History taking of concomitant medication is standard procedure for all patients admitted at Lade Behandlingssenter. All concomitant medication (incl. vitamins, herbal preparation and other “over-the-counter” drugs) used by the subject of treatment start will be recorded in the CRF.

**Laboratory analysis**

Blood samples will be obtained at time of admittance to determine subjects’ overall clinical status (CRP, Hb, HCT, WBC (incl.differential counting, Na, K, Ca, glucose, creatinine, ALAT, LD, ALP, γGT, INR, albumin, bilirubin), p-oxytocin and toxicology (including the ethanol markers CDT and PEth – in addition to EtG and EtS in urine). Pregnancy test (HCG) is taken at admittance in fertile women. Urine dipstick is a part of standard procedure in all patients.

### Treatment Start, D1

Since patients are likely to experience alcohol abstinence, they will undergo CIWA-Ar registrations as described in section 7.2. Medication for abstinence (benzodiazepines in the form of oxazepam) is given based on CIWA-Ar-scores. Study subjects will receive the first dose of nasal spray shortly thereafter, while following the standard procedures for abstinence treatment. Study subjects receive the Actigraph to be carried throughout the stay.

### During Treatment, D1-D3

CIWA-Ar registrations are performed to monitor abstinence severity; these measturements include blood pressure and heart rate. Since CIWA-Ar is symptom driven, there are no exact times for these measurements. Nasal spray is given twice daily, at 0900h and at 1800h. The nasal spray container is weighed at the end of the inpatient period.

Day 3; at discharge: Actigraphs are handed in. Blood and urine samples are obtained. Patients are asked to fill out questionnaires at day 3, see table in section 7.3. Patients are instructed in the use of nasal spray as needed for the next 4 weeks. They will receive a notebook in which they will keep a log of use of the study drug, any intake of concomitant medication etc., and possible adverse events.

### End of Treatment and End of Study Visit, D 30

Clinical status with vital signs and laboratory tests is repeated. Patients fill out questionnaires (see table in section 7.3), and hand in nasal sprays and their notebooks. Nasal spray containers are weighed. A phone interview will be done at day 60.

### Withdrawal Visit

If the patient is withdrawn from the study before completing the study by his/her own will, 3 attempts to reach subject for is made (e.g telephone, mail).Patients withdrawing from the study will go back to standard procedures for the follow-up treatment at Lade Behandlingssenter. Because of no expected side effects and the short half-life of oxytocin, no further examinations or tests are considered needed. The nasal sprays are to be returned to Lade Behandlingssenter.

## Criteria for Patient Discontinuation

Patients may be discontinued from study treatment and assessments at any time. Specific reasons for discontinuing a patient for this study are:

- Voluntary discontinuation by the patient who is at any time free to discontinue his/her participation in the study, without prejudice to further treatment.
- Safety reason as judged by the Principal Investigator
- Major protocol deviation, which would be not following guidelines of CIWA-Ar and medication or not following guidelines for nasal spray doses.
- Incorrect enrolment ie, the patient does not meet the required inclusion/exclusion criteria for the study
- Patient lost to follow-up
- A female patient becoming pregnant
- Deterioration in the patients condition which in the opinion of the Principal Investigator warrants study medication discontinuation (to be records as an AE or under Investigator Discretion)
- Patient’s non-compliance to study treatment and/or procedures

## Procedures for Discontinuation

### Patient Discontinuation

Patients who withdraw or are withdrawn from the study, will discontinue treatment with oxytocin. They will however continue their treatment for alcohol addiction at Lade Addiction Treatment Center. If possible, a final assessment will be performed (end of study visit or by phone). The reason for discontinuation will be recorded, if the patient gives any. The investigator is obliged to follow up any significant adverse events until the outcome either is recovered or resolved, recovering/resolving, not recovered/not resolved, recovered/resolved with sequelae, fatal or unknown.

Patient`s who withdraw or are withdrawn from the study before start of treatment, will be replaced.

### Trial Discontinuation

The whole trial may be discontinued at the discretion of the PI or the sponsor in the event of any of the following:

- Occurrence of AEs unknown to date in respect of their nature, severity and duration
- Medical or ethical reasons affecting the continued performance of the trial
- Difficulties in the recruitment of patients

The sponsor and principal investigator will inform all investigators, the relevant Competent Authorities and Ethics Committees of the termination of the trial along with the reasons for such action. If the study is terminated early on grounds of safety, the Competent Authorities and Ethics Committees will be informed within 15 days.

## Laboratory Tests

Bloodsamples, urine samples: Sample collection, handling and analysis will be performed in accordance with hospital/laboratory standard procedures at St. Olavs Hospital.

# assessments

## Assessment of Efficacy Response

Efficacy response is measured as the total number of mg of oxazepam used by study subjects undergoing detoxification based on a symptom-driven protocol using CIWA-Ar scores (see Section 7.2). The dosages of oxazepam and the CIWA-Ar-scores are registered in the CRF.

Actigraph-assessed akathisia and self-reported sleep will also be compared with CIWA-Ar scores and oxazepam dosages retrospectively.

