# STUDY OBJECTIVES and related endpoints

## Primary Endpoint

| Phase 1: Milligrams of benzodiazepines (oxazepam) used to complete 3 days of detoxification and Actigraph-assessed akathisia and sleep.  Phase 2: Time to ‘relapse’ and amount of alcohol intake during 4 weeks of subsequent outpatient treatment. |
| --- |

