## Population for Analysis

The following populations will be considered for the analyses:

- Intention to treat (ITT) population: Includes all randomized participants, regardless of protocol adherence.
- Per-protocol population (PP): Includes all randomized participants showing full protocol adherence.
- Safety population: Includes all subjects who have received at least one dose of study medication. Subjects who withdraw from the study will be included in the safety analysis. A list of withdrawn subjects, preferably with the reasons for withdrawal, will be made.

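### Section 6.3 lets patients be taken off assessments as well as treatment, so the 3-day oxazepam total can be lost or cut short for patients whom the intention-to-treat analysis must include

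*Protocol*

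**What the plan says.** **Outcome.** Section 7.1 of the Protocol defines the efficacy measure: "Efficacy response is measured as the total number of mg of oxazepam used by study subjects undergoing detoxification". Section 2.1 words the phase 1 endpoint as "Milligrams of benzodiazepines (oxazepam) used to complete 3 days of detoxification and Actigraph-assessed akathisia and sleep". Section 10.4 compares oxazepam in mg at 3 days by Student's t-test.

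**Exit.** Section 6.3 opens: "Patients may be discontinued from study treatment and assessments at any time". Its reasons include the patient's own choice, non-compliance with treatment or procedures, "Major protocol deviation, which would be not following guidelines of CIWA-Ar and medication or not following guidelines for nasal spray doses", and "Deterioration in the patients condition which in the opinion of the Principal Investigator warrants study medication discontinuation".

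**After exit.** For patients who withdraw by their own will, section 6.2.4 says that "no further examinations or tests are considered needed", and gives the lack of expected side effects and the short half-life of oxytocin as the reason. Section 6.4.1 says: "If possible, a final assessment will be performed (end of study visit or by phone"). It adds that withdrawn patients stop oxytocin but go on with their addiction treatment at the centre. Only those who withdraw before treatment starts are replaced.

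**Population.** Section 10.3 defines the intention-to-treat set: "Includes all randomized participants, regardless of protocol adherence". The per-protocol set requires full adherence.

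**The concern.** Oxazepam is given repeatedly in response to CIWA-Ar scores, so the total grows with time under observation. A patient who stops being observed on day 1 has a small recorded total whatever the underlying need. The reasons for exit in section 6.3 are not neutral. Deterioration, non-compliance and departure from the CIWA-Ar or medication guidelines can all depend on how severe the withdrawal is, and the last of these acts on the very process that generates the primary outcome.

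The protocol therefore promises an analysis of all randomised patients regardless of adherence, while permitting outcome collection to stop because of poor adherence. If that happens, the primary comparison rests on missing or shortened totals in arms of about 20. The remark in section 10.4 that mixed models lessen concern about missing data does not help here. It refers to the models for sleep, actigraph scores, anxiety, depression and alcohol use, not to the t-test on a single total.

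**Working it through.** **Inputs from the Protocol, section 10.1:** mean about 20-30 mg, SD about 10 mg, usual range 0-60 mg, target difference 10 mg, alpha 0.05, power 80%, 16 per group required, 40 enrolled. With 1:1 allocation that is 20 per arm. No dropout rate is stated.

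**Assumptions, not in the Protocol:** how many leave before day 3, how they split between arms, and what share of their dose goes unrecorded.

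**1. The plan's own figure.** n per arm = 2 × (1.960 + 0.842)² × (10/10)² = 15.70, rounded up to 16. It reproduces, so the sample size is not at issue.

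**2. If partial totals are analysed as 3-day totals.** Fall in an arm's mean = proportion leaving × leavers' mean need × share unrecorded.
- Leavers of average need: 4/20 × 25 mg × 0.5 = 2.5 mg, which is 25% of the 10 mg target.
- Leavers needing 40 mg: 4/20 × 40 mg × 0.5 = 4.0 mg, which is 40% of the target.
- Same exit in both arms, no true effect: 2.5 − 2.5 = 0 mg.

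**3. If leavers are dropped.** Take an arm of 20 whose true mean is 25 mg.
- Leavers of average need: no shift in the mean, only a smaller arm.
- Four leavers needing 40 mg: the other 16 average (20 × 25 − 4 × 40)/16 = 340/16 = 21.25 mg, a fall of 3.75 mg.

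Dropping leavers is therefore no protection when exit depends on severity, and it also departs from section 10.3.

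**4. Range for the partial-total case, exits in the oxytocin arm only.**
- Smallest: mean 20 mg, 10% leaving, 67% of the dose used before exit: 20 × 0.10 × 0.33 = 0.66 mg.
- Largest: mean 30 mg, 30% leaving, 33% used before exit: 30 × 0.30 × 0.67 = 6.03 mg.

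**5. Effect on the t-test.** Simulation with gamma-distributed totals, SD 10 mg, 20 per arm, two-sided 0.05, 40,000 runs, exit unrelated to need:

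| Scenario | Observed difference | Chance of a significant result favouring oxytocin |
| --- | --- | --- |
| No true effect, no exit | 0 mg | about 2.5% |
| No true effect, 20% exit in both arms | 0 mg | about 2.5% |
| No true effect, 20% exit in oxytocin only, half used, mean 25 mg | 2.5 mg | 11.8% |
| No true effect, whole range in step 4 | 0.7 to 6.0 mg | 4% to 38% |
| True effect (20 vs 30 mg), no exit | 10.0 mg | 86% |
| True effect, 20% exit in placebo only, half used | 7.0 mg | 54% |
| True effect, 20% exit in both arms, half used | 9.0 mg | 75% |

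The placebo-only row follows from 30 − 0.20 × 30 × 0.5 = 27 mg, and 27 − 20 = 7 mg. With exit in both arms, 27 − (20 − 0.20 × 20 × 0.5) = 27 − 18 = 9 mg. Balanced exit is thus harmless under the null but still shrinks a real effect.

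**The case against.** A reader might infer that the plan is set up to score early exit as efficacy. The Protocol does not support that. No sentence says that a leaver's partial total enters the t-test. Section 2.1 speaks of the amount used to complete 3 days, which can be read to mean that a non-completer has no value at all. Nor does anything in the text predict more exit in the oxytocin arm.

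Other counter-arguments also stand, in part:
- Section 7.2 has all benzodiazepine doses documented with the CIWA-Ar scores, section 9.2 requires treatments given to be in the medical record, and section 9.3 has the primary endpoint fully monitored. A patient taken off the spray who stays on the ward will probably have a complete chart. It would therefore be too strong to say that intention-to-treat cannot be delivered; the exposure is mainly to patients who physically leave within three days.
- The sentence in section 6.2.4 gives a safety rationale and concerns own-will withdrawal. It need not contradict the final assessment in section 6.4.1.
- Section 6.3 covers the whole study. Some of its reasons, such as loss to follow-up or pregnancy, mainly concern the outpatient phase, after the oxazepam total is complete.
- How to impute or rank non-completers is ordinary content for a statistical analysis plan, which may exist.

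What these points do not answer is that section 6.3 names assessments alongside treatment, and that no section says study recording of oxazepam continues to day 3 once a patient is discontinued. An analysis plan cannot recover outcomes that the protocol does not require to be collected.

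**Conclusion.** The point holds as a conflict between the rule on discontinuation and the stated analysis population. Under sections 6.3, 6.2.4 and 6.4.1, primary-outcome data may stop for reasons tied to adherence and symptoms, while section 10.3 promises every randomised patient regardless of adherence. The resulting bias has no fixed direction: more or earlier exit under oxytocin can mimic a benefit, and more or earlier exit under placebo can hide one.

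The size cannot be derived from the Protocol. The 2.5 mg and 4 mg shifts, 25% and 40% of the 10 mg target, assume four leavers in one arm, none in the other and half the dose unrecorded. Under the null, balanced exit gives about zero. Three supervised inpatient days may keep the number of leavers small, but with 20 per arm each leaver is 5% of an arm.

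**What to change.** - **Sections 6.3 and 6.4:** separate stopping the spray from leaving the study. Every randomised patient keeps oxazepam recording for days 1 to 3 and the day 30 and day 60 contacts unless consent is withdrawn. The reasons for stopping treatment need not change.
- **Section 6.2.4:** align with this, for instance by limiting the sentence on further tests to safety examinations.
- **Section 10.4:** state that a partial total from a patient who leaves before day 3 is treated as incomplete and not analysed as a full 3-day total, and that a sensitivity analysis for leavers will be done. The method can be left to the statistical analysis plan.

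The cost is amendment wording, one sensitivity analysis and modest follow-up effort for the few who stop early. The doses are already charted, so little new data collection is needed on the ward.

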## Safety and Tolerability Assessments

Safety will be monitored by the assessments described below as well as the collection of AEs at every visit. Significant findings that are present prior to the signing of informed consent must be included in the relevant medical history/ current medical condition page of the CRF. For details on AE collection and reporting, refer to Section 8.4.

For the assessment schedule refer to Flow chart in Section 6.1.

**CIWA-Ar**

CIWA-Ar has 10-items assessing headache, visual and tactile and auditory disturbances, paroxysmal sweats, orientation and clouding, agitation and anxiety (all assessed on a 0-7 severity scale). It also includes blood pressure, pulse, respiration rate, temperature. A symptom-driven protocol of PRN administrations of oxazepam will be followed to all included patients while undergoing detoxification. Symptom-triggered benzodiazepine treatment has been shown to require less total medication compared to fixed regimen benzodiazepine tapers ^22^. A ‘‘standing order set’’ to administer oxazepam based on a patient’s CIWA-Ar score will as such be followed. Mild CIWA-Ar scores (0 to 9)^3^ indicate mild withdrawal symptoms and indicate no benzodiazepine treatment (reassessed in 4 hours). A CIWA-Ar score of 10 to 14 represents moderate withdrawal and 10 mg oxazepam will be given orally as needed, scores reassessed after 1 hour. Severe withdrawal is represented by a score 15 and above and indicate oxazepam 15 mg given orally as needed, scores reassessed after 1 hour. All benzodiazepines (dosage and amount) will be documented along with CIWA-scores.

Laboratory evaluation:

St. Olav’s University Hospital, department of medical biochemistry will be used for the analysis of hematology and biochemistry specimens collected, except plasma-oxytocin which is sent to the Hormonlaboratoriet at Oslo Universitetssykehus.

Hematology assessments will include the following parameters: hemoglobin, platelets, CRP, HCT, WBC (incl.differential counting,

Blood chemistry assessments will include the following: albumin, creatinine, Na, K, Ca, glucose, ALAT, LD, ALP, γGT, INR, bilirubin, p-oxytocin, CDT, PEth, HCG (in fertile women).

Urine analysis will include a toxicological screening including ethanol metabolites - EtG and EtS.

